### Primary outcomes

Primary outcomes are overall average knee pain severity in the last week measured on an 11-point numeric rating scale (NRS), where 0 = ‘no pain’ and 10 = ‘worst pain possible’ [58], and physical function assessed using the physical function subscale of the Western Ontario and McMaster Universities (WOMAC) Osteoarthritis Index [59]. The WOMAC is a disease-specific self-report instrument which has demonstrated validity, reliability, and responsiveness [60]. The physical function subscale contains 17 questions scored from 0 to 4, giving a range of possible scores from 0 (no dysfunction) to 68 (maximum dysfunction).

### Secondary outcomes

Secondary outcome measures include:
i)Self-reported weight, measured in kilograms. Participants are asked to use the same set of scales for these measures across the time points;ii)Physical activity, assessed using the Incidental and Planned Exercise Questionnaire (IPEQ-W) [61];iii)Health-related quality of life, measured using the Assessment of Quality of Life Instrument (AQoL-8D) [62];iv)Global rating of change, scored on a 7-point Likert scale for “Overall change in your study knee since you began the study” from “much worse” to “much better” [63];v)Satisfaction with care, scored on a 7-point Likert scale for “Overall satisfaction with the care you received in this study” from “extremely unsatisfied” to “extremely satisfied”;vi)Self-reported appointments with an orthopaedic surgeon;vii)Depression, anxiety, and stress, measures on the Depression, Anxiety, and Stress Scale (DASS-21) [64];viii)Self-reported total knee joint replacement and knee arthroscopy surgery;ix)Willingness to undergo surgery, measured on a 5-point Likert scale ranging from “definitely not willing” to “definitely willing”.

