### Participants

A total of 415 participants who have private health insurance with Medibank Private at a level that includes cover for arthroplasty surgery are recruited from around Australia. Medibank Private is one of Australia’s largest health funds, with 3.7 million members across Australia [38]. Inclusion and exclusion criteria are outlined in Table 1. Medibank Private send targeted invitations, predominantly via email, to potentially eligible members. They also advertise the study in their member newsletters and on their website. The University of Melbourne manage the clinical screening of volunteers. Screening occurs via a two-step process; i) via an online survey and, if eligible, ii) via additional telephone screening by research personnel at The University of Melbourne. Additional clearance to participate is sought from a general practitioner for anyone who does not pass pre-exercise screening questions [40], reports more than 1 fall in the past 12 months, or is house-bound due to mobility limitations (e.g. concurrent disabling low back pain).

**Table 1 Tab1:** Participant eligibility criteria

Inclusion criteria	Exclusion criteria

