### Data collection and management

Data are collected via online questionnaire and stored on a secure password-protected server. The “study knee” is the painful knee or, in people with bilaterally eligible knees, the most painful knee.

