**Secondary outcome measures**				
Weight	Self-reported	✓	✓	✓
Physical activity	IPEQ-W questionnaire	✓	✓	✓
Health-related quality of life	AQoL-8D questionnaire	✓	✓	✓
Perceived change since baseline	Overall change, 7-point ordinal scale		✓	✓
	Change in pain, 7-point ordinal scale		✓	✓
	Change in function, 7-point ordinal scale		✓	✓
	Change in physical activity, 7-point ordinal scale		✓	✓
Satisfaction with care	7-point ordinal scale		✓	✓
Appointment with orthopaedic surgeon	Yes/No	✓	✓	✓
Depression, anxiety, and stress	DASS-21	✓	✓	✓
Surgery performed	Self-reported TKJR and arthroscopy		✓	✓
Willingness to undergo surgery	5-point ordinal scale	✓	✓	✓

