### Additional measures

*Economic data*: assessed by self-reported medication use and healthcare costs (regarding the use of health services), quality-adjusted life years (QALY), cost-effectiveness ratio (calculated using predictions of health care costs and QALYs), and work productivity (using the World Health Organisation Health and Work Performance Questionnaire [70]). Knee surgery costs will be obtained by linking to Medibank data.

*Adverse events*: any undesirable clinical occurrence, whether considered to be treatment-related or not, that includes a clinical sign, symptom, or condition, are self-reported in questionnaires and recorded by the clinician during the consultation. Participants are asked to provide details on the nature of the event, how long it lasted for, and what action they took.

*Adherence*: assessed by recording the number of consultations received from the physiotherapist and/or dietitian. Adherence to prescribed exercise and physical activity programs is self-reported by the participant via questionnaire, being scored on an 11-point NRS (0 = not at all and 10 = completely as instructed). Adherence to the weight management plan, if applicable, is also self-reported and scored on a similar 11-point NRS.

*Perceived usefulness of treatment components*: assessed by self-report with response options ranging from 0 = “not at all” to 10 = “extremely useful”. Usefulness questions relate to the information on the website, consultations with the physiotherapist and/or dietitian, resource booklets, Fitbit, VLCD, strengthening exercise program, and physical activity plan. Participants will also be asked how many times they accessed the website in the last 6-months (5-point scale ranging from “never” to “> 10 times”) and how easy it was for them to use the videoconferencing software (11-point NRS ranging from 0 = “not at all easy” to 10 = “extremely easy”).

*Long-term surgical rates*: via linkage with the data routinely collected by Medibank Private, and will include the number of individuals who had a knee arthroscopy and/or arthroplasty intervention at 2 and 5 years after baseline. These findings will be reported separately from the main trial outcomes.

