### Analysis

We will use intention-to-treat analyses, using multiple imputation to account for missing data and details on the imputation will be reported [74]. Participants will be included in their randomised treatment groups regardless of their post-randomisation behaviour. *P* values less than 0.05 will be considered significant. Outcomes (primary, secondary, and determinants) will be compared between groups as follows: i) *Exercise* vs *Exercise plus weight management*; ii) *Exercise* vs control, and; iii) *Exercise plus weight management* vs control. For continuous data, mean differences in change over time between these groups will be estimated using linear regression models fit to data from both follow-up time points, with random effects for participants, and accounting for clustering by physiotherapist and dietitian in the *Exercise* and *Exercise plus weight management* groups. Models will be adjusted for the stratification variable (history of knee surgery) and values of the outcome at baseline. Terms for time and treatment will be included, with an interaction between the two. Regression assumptions will be assessed using standard diagnostic plots. For binary outcomes, logistic regression models will be fit using generalised estimating equations to account for clustering, with risk differences and 95% confidence intervals calculated. This will include a comparison of the proportion of participants in each group whose improvement meets or exceeds the minimal clinically important difference for each of the primary outcomes. For ordinal outcomes, proportional odds models will be fit similarly. Multinominal models will be applied if the assumption of proportional odds is not valid. To assess the sensitivity of the results for the primary outcomes in situations in which the outcomes are missing not at random, we will apply a pattern-mixture approach that involves fitting regression models that adjust for departures from the missing at random assumption [75].

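### Knee surgery at 6 and 12 months is defined by self-report alone, and the planned insurer linkage is not used to complete or verify it

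*Protocol article*

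**What the plan says.** All points are from the Protocol article.

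- **Outcome.** Item viii under Secondary outcomes is "Self-reported total knee joint replacement and knee arthroscopy surgery". Table 4 gives the instrument as "Self-reported TKJR and arthroscopy", at 6 and 12 months.
- **Collection.** Data collection and management states: "Data are collected via online questionnaire and stored on a secure password-protected server".
- **Missing data.** The Analysis section opens with "We will use intention-to-treat analyses, using multiple imputation to account for missing data". It then sets its scope: "Outcomes (primary, secondary, and determinants) will be compared between groups as follows". Surgery is a secondary outcome and no exception is made for it. The pattern-mixture analysis for data missing not at random is limited to the primary outcomes.
- **Second source.** Under Additional measures, "Knee surgery costs will be obtained by linking to Medibank data". The same section takes arthroscopy and arthroplasty counts at 2 and 5 years after baseline from the insurer's routine data, to be reported separately from the main results.
- **Population.** Participants are recruited with "private health insurance with Medibank Private at a level that includes cover for arthroplasty surgery".

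Nowhere does the article say that linked data will complete or check the 6- and 12-month surgery outcome.

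**The concern.** The plan provides for two records of knee surgery over the first year and uses only the weaker one for the clinical outcome. Health care use is compared from baseline to 12 months, so claims obtained for surgery costs should cover the same window. The 2-year count runs from baseline and, read as cumulative, also includes year one.

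Two things are at stake. The first is precision: a participant who stops answering has no status, although the claims might show whether an operation took place. The second is bias: having an operation is a plausible reason to stop answering knee questionnaires. Imputation under missing-at-random could then understate surgery, and no stated sensitivity analysis would reveal it for this outcome. The 12-month figure (self-report) and the 24-month figure (claims) would also come from different sources and need not agree.

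**Working it through.** **1. The plan's own figure.** Inputs from Trial sample size and the randomisation section: effect sizes 0.3 (between treatments) and 0.4 (against control), baseline to follow-up correlation 0.4, power 80%, two-sided 0.05, loss 15%, allocation 5:5:2. The residual SD is √(1 − 0.4²) = 0.917.

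- Treatment arms: 2 × [0.917 × (1.960 + 0.842) / 0.3]² = 146.5, so 147; 147 / 0.85 = 172.9, so 173.
- Control: (1 + 1/2.5) × [0.917 × 2.802 / 0.4]² = 57.7, so 58; 58 / 0.85 = 68.2, so 69.
- Total: 2 × 173 + 69 = 415. This matches the article and confirms that the 15% applies to every arm.

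**2. Participants without a self-reported status.** This assumes that the 15% holds at the time point concerned.

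- Each treatment arm: 0.15 × 173 = 25.95, about 26.
- Control: 0.15 × 69 = 10.35, about 10.
- Total: 0.15 × 415 = 62.25, about 62.

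**3. Operations that could lie among them.** The article gives no surgery rate, so rates of 2% to 15% are assumed, equal in responders and non-responders. Expected operations = 62.25 × rate:

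| Assumed rate | Expected operations |
|---|---|
| 2% | 1.2 |
| 5% | 3.1 |
| 10% | 6.2 |
| 15% | 9.3 |

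One event in the control arm is 1/69 = 1.4 percentage points.

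**4. Precision.** The 95% half-width for *Exercise* against control is 1.96 × √[p(1 − p)(1/n₁ + 1/n₂)].

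| Assumed rate | 85% observed (147.05 and 58.65) | All observed (173 and 69) |
|---|---|---|
| 5% | 6.6 points | 6.1 points |
| 10% | 9.1 points | 8.4 points |

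The ratio is 1/√0.85 = 1.085, so intervals are about 8% wider.

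**5. Bias, illustration only.** Suppose that in one arm 5% of responders and 10% to 15% of non-responders have surgery. The true risk is 0.85 × 5% + 0.15 × 10% = 5.75%, up to 0.85 × 5% + 0.15 × 15% = 6.5%. Imputing at the responder rate gives 5%, a shortfall of 0.75 to 1.5 points in that arm. The error in the risk difference is the difference between the two arms' shortfalls: nil if they are equal, and up to 1.5 points if only one arm has the excess.

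**The case against.** The strongest reply is that the article is clear and consistent in defining this outcome by self-report, and that imputation of surgery follows from one general sentence. Which variables are imputed, and with what auxiliary data, may be settled in an analysis plan that is not shown. That stands as a limit: the point is about the chosen outcome source, which the article does fix, and not about missing imputation detail.

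Second, claims-based surgery is analysed elsewhere. The 2- and 5-year counts have their own logistic model, and a cumulative 2-year count would pick up first-year operations. This reduces the loss but does not remove it, since those results are reported separately and do not supply the 6- and 12-month comparison.

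Third, imputation need not be at the responder rate. Willingness to undergo surgery and appointments with a surgeon are measured and could inform it, which makes missing-at-random more plausible. People booked for knee surgery are excluded at entry, which may keep the rate low. Imprecision dominates in any case: in the illustration, at most 1.5 points of bias against a half-width of 6.6. All of this stands.

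Fourth, combining sources gives responders two chances of detection and non-responders one. That is a real cost, taken up under the fix.

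A reader might infer more than the text supports:

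- *That every participant is already linked.* Linkage is stated as a future step, without coverage. Membership at entry does not show continued membership or consent to linkage.
- *That known events are replaced by guesses.* Imputation fills missing answers and overwrites no recorded one.
- *That the economic results become inconsistent.* The stated ratios use improvement in pain and function, and quality-adjusted life years; surgery is not an effect measure in them.
- *That reducing surgery is a central aim.* The hypotheses concern pain and function; surgery is one of nine secondary outcomes.

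**Conclusion.** The point holds as a cheap improvement to one secondary outcome. By its definition the 6- and 12-month surgery outcome depends on a questionnaire answer. At the planned 15% loss about 62 of 415 participants would lack one and, as the article is worded, would be imputed, with no missing-not-at-random check for this outcome. A second record of the same kind of event is planned and left unused here.

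The count of 62 rests on the article's loss figure, applied equally to all arms. The 8% widening follows from that figure alone; the half-widths in points also need an assumed rate. In the illustration the 0.75 to 1.5 point shortfall is a relative understatement of 13% (0.75/5.75) to 23% (1.5/6.5). A reader might take this as an estimate of the bias. It is not: it depends on assumed rates, concerns one arm, and partly or wholly cancels in the contrast if drop-out behaves alike across arms. The actual bias cannot be computed from the article. The primary analysis, the sample size and the stated cost-effectiveness ratios are unaffected.

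**What to change.** Amend the definition of the surgery outcome along these lines:

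1. Surgery by 6 and by 12 months is a knee arthroplasty or arthroscopy that is reported in the questionnaire or recorded in linked insurer claims dated within the window.
2. Impute only participants with neither a questionnaire answer nor usable linkage, for example because membership lapsed or linkage was not consented to.
3. Report self-report alone and claims alone as sensitivity analyses.

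The cost is a short change to the outcome definition and a merge with data that the plan already intends to obtain. If all participants can be linked, the number left to imputation falls from about 62 towards zero; the article does not state how many can be.

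The downside is that claims miss operations funded outside the insurer, and the cover criterion names arthroplasty only although the outcome includes arthroscopy. A linked non-responder operated on elsewhere would count as having had no surgery, so non-responders may be slightly under-ascertained, and unequally so if drop-out differs by arm. The claims-only analysis applies one source to all arms and so checks this.

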### Descriptive data

At baseline, descriptive data is collected, including: i) age; ii) gender; iii) height and weight; iv) country of birth; v) postal code; vi) Aboriginal or Torres Strait Islander Heritage; vii) education level; viii) current employment status; ix) duration of symptoms; x) length of time since first visit to a doctor for knee pain; xi) previous history of knee arthroscopy and arthroplasty; xii) pain in other parts of the body; xiii) expectation of treatment outcomes, and; xiv) medication use.

### Determinants

i)Self-efficacy for managing arthritis symptoms, measured using the Arthritis Self-Efficacy Scale [65];ii)Self-efficacy for eating control, measured using the Weight Efficacy Lifestyle Questionnaire [66];iii)Attitudes towards self-management, measured using the Patient Activation Measure (PAM-13) [67];iv)Treatment beliefs about arthroplasty, using the Treatment beliefs in knee and hip OsteoArthritis (TOA) questionnaire – Arthroplasty subscale [68];v)Fear of movement, measured using the Brief Fear of Movement Scale for osteoarthritis [69].

### Additional measures

*Economic data*: assessed by self-reported medication use and healthcare costs (regarding the use of health services), quality-adjusted life years (QALY), cost-effectiveness ratio (calculated using predictions of health care costs and QALYs), and work productivity (using the World Health Organisation Health and Work Performance Questionnaire [70]). Knee surgery costs will be obtained by linking to Medibank data.

*Adverse events*: any undesirable clinical occurrence, whether considered to be treatment-related or not, that includes a clinical sign, symptom, or condition, are self-reported in questionnaires and recorded by the clinician during the consultation. Participants are asked to provide details on the nature of the event, how long it lasted for, and what action they took.

*Adherence*: assessed by recording the number of consultations received from the physiotherapist and/or dietitian. Adherence to prescribed exercise and physical activity programs is self-reported by the participant via questionnaire, being scored on an 11-point NRS (0 = not at all and 10 = completely as instructed). Adherence to the weight management plan, if applicable, is also self-reported and scored on a similar 11-point NRS.

*Perceived usefulness of treatment components*: assessed by self-report with response options ranging from 0 = “not at all” to 10 = “extremely useful”. Usefulness questions relate to the information on the website, consultations with the physiotherapist and/or dietitian, resource booklets, Fitbit, VLCD, strengthening exercise program, and physical activity plan. Participants will also be asked how many times they accessed the website in the last 6-months (5-point scale ranging from “never” to “> 10 times”) and how easy it was for them to use the videoconferencing software (11-point NRS ranging from 0 = “not at all easy” to 10 = “extremely easy”).

*Long-term surgical rates*: via linkage with the data routinely collected by Medibank Private, and will include the number of individuals who had a knee arthroscopy and/or arthroplasty intervention at 2 and 5 years after baseline. These findings will be reported separately from the main trial outcomes.

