### Information only (control) group

The information only (*Control*) group receive information, advice, and education about OA and its management via a bespoke website developed by the research team which is only accessible via password login. The website includes: i) educational information including understanding OA, recommended treatment options (including a total knee replacement decision aid), exercise and physical activity, weight loss, understanding and managing pain (including audio files to facilitate mini-relaxations and pleasant imagery), sleep, and “success stories” from other people with knee OA, and; ii) links to recommended external websites for further help and support (e.g. MyJointPain, painHEALTH, Musculoskeletal Australia). Participants have access to the study website from enrolment to completion of the 12-month follow-up questionnaire.

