### Exercise intervention

The *Exercise* intervention consists of educational information and links to external websites as for the *Control* group (bespoke website, in addition to exercise modules related only to this intervention) plus six individual consultations with a physiotherapist via videoconferencing over the internet (Zoom Video Communications Inc., California USA) over 6-months (Table 2). The physiotherapist consultations include individualised advice on treatment options, decision support, a structured exercise and physical activity plan, behaviour change support, and facilitation of other self-management strategies including pain coping skills training. Educational resources (Table 2) are provided in hardcopy via post and electronically via the study website. Participants are also posted three exercise resistance bands (green, red, and blue) for strengthening exercises and a Fitbit (Flex 2 model) to help track and monitor physical activity.

**Table 2 Tab2:** Summary of resources provided to participants in the *Exercise* and *Exercise plus weight management* groups

Resource	Description of content/purpose	***Exercise*** group	***Exercise plus weight management*** group
Study website	Information about OA, treatment options, exercise and physical activity, weight loss, managing pain, sleep, and stories from other people with knee OA	√	√
Consultations with a physiotherapist	6 video consultations over 6-months. Advice on treatment options, structured exercise and physical activity plan, and behaviour change support	√	√
Consultations with a dietitian	6 video consultations over 6-months. Helps participant undertake VLCD with behaviour change support		√
Exercise bands	3 exercise resistance bands (green, red, and blue) for strengthening exercises	√	√
Activity tracker (Fitbit)	To help track and monitor physical activity	√	√
Plastic portion plate	To help manage portion sizes		√
Optifast® meal replacements	6-months’ worth of meal replacements for the VLCD		√
Educational video about the VLCD	Short video about the VLCD featuring endocrinologists and dietitian experts, and a person with knee OA		√

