### Exercise plus weight management intervention

Participants who are allocated to the *Exercise plus weight management* intervention receive all components of the *Exercise* intervention plus 6 individual videoconferencing consultations with a dietitian (over 6 months) who helps the participant undertake a weight management program involving a ketogenic very low calorie diet (VLCD) [50]. This diet was chosen as it has been shown to lead to greater weight loss in the short-term when compared to low-fat diets [51, 52] and the release of ketones, produced by the liver during fatty acid oxidation while fasting or on a diet that restricts carbohydrates, can help suppress appetite and contribute to further weight loss [50]. Participants are provided with Optifast® meal replacements (Nestlé Health Science, Rhodes, Australia) (or Optislim® [OptiPharm Pty Ltd., Clayton, Australia] if unavailable or the participant is vegetarian) and additional educational resources to support their weight loss (Table 2). Participants are encouraged to lose at least 10% or more of their body weight, as this has been associated with clinically important improvements in pain [53, 54].

In addition to the five educational booklets provided in the *Exercise* intervention, participants in the *Exercise plus weight management* intervention are provided with four additional booklets (described in Table 2). Participants are also mailed a plastic “portion plate” (https://www.nestle.com.au/nhw/nestle-portion-plates) to help them manage meal portion sizes. A short educational video about the VLCD featuring endocrinologists and dietitian experts, and a person with knee OA, is also available on the study website.

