### Dealing with adverse events

Expected adverse events include: i) transient increase in knee pain or swelling due to increased exercise or physical activity; ii) feeling hungry, fatigued, fuzzy-headed, and/or having headaches, and either diarrhoea or constipation during the first week after commencing the VLCD. Participants are advised to report any adverse events to the study coordinator as soon as they can, which will be documented in treatments notes and an adverse events log. If necessary, treatment is discontinued and further medical advice is arranged. Adverse events are also collected via self-report in the 6- and 12-month questionnaires.

Clinicians are instructed to report any adverse events to the trial coordinator, record the event in their consultation notes, and refer participants to their general practitioner if necessary. Participants are provided with a “help” email address to contact if they have any issues with their exercise/physical activity or weight management program in between consultations. The email is monitored daily by research staff and, if necessary, staff can seek further advice/guidance from the participant’s physiotherapist and/or dietitian.

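### Adverse events are gathered from sources that differ by arm (up to 12, 6 and 0 planned clinician consultations), so a by-arm count pooled over sources would be expected to overstate harm in the active arms

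*Protocol article*

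**What the plan says.** The Additional measures section defines an adverse event broadly, as "any undesirable clinical occurrence, whether considered to be treatment-related or not". It gives two sources for the measure: events "are self-reported in questionnaires and recorded by the clinician during the consultation".

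The section Dealing with adverse events describes three routes.
- **Questionnaires, all arms:** "Adverse events are also collected via self-report in the 6- and 12-month questionnaires".
- **Clinicians, where there is one:** "Clinicians are instructed to report any adverse events to the trial coordinator, record the event in their consultation notes".
- **Coordinator, no arm restriction stated:** participants are advised to tell the study coordinator promptly, and these reports go into an adverse events log.

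Exposure to clinicians differs by design. The Exercise arm has "six individual consultations with a physiotherapist via videoconferencing over the internet". The combined arm has those six plus six with a dietitian (section Exercise plus weight management intervention). Controls "receive information, advice, and education about OA and its management via a bespoke website developed by the research team", and no consultation is described for them.

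Table 4 lists harms among the other measures at 6 and 12 months. It does not attach either of the footnotes that mark measures taken only in the active arms. The Analysis section compares primary outcomes, secondary outcomes and determinants between groups, and adverse events are in none of these classes.

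**The concern.** One of the two sources that make up the measure exists only in the active arms, and it is twice as dense in the combined arm as in Exercise. If true event rates were equal, a count over all sources would still be expected to rise from control to Exercise to combined.

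Recall at 6 months is unlikely to level this out. The expected events that the protocol lists are short-lived: temporary knee pain or swelling, and symptoms in the first week of the diet. Physiotherapy consultations are recommended between weeks 1 and 21, and the first dietitian consultation falls in the same week as the first physiotherapy one. A control participant with a brief flare is first asked systematically at 6 months. Because the definition does not require a causal link to treatment, unrelated background events are affected as well.

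The trial is meant to inform whether a diet component should be added to a remotely delivered exercise service. A harms table inflated by contact frequency would bear on exactly that question.

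**Working it through.** The protocol states no adverse event rate and no capture rate, so there is no figure of its own to reproduce. The check has two parts.

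**1. Scheduled contacts at which an event can be captured** (control : Exercise : combined)

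| | Control | Exercise | Combined |
|---|---|---|---|
| Clinician consultations | 0 | 6 | 6 + 6 = 12 |
| Questionnaires over 12 months | 2 | 2 | 2 |
| Total over 12 months | 2 | 8 | 14 |
| Total up to and including the 6-month questionnaire | 1 | 7 | 13 |

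Restricted to the questionnaires, the counts are 2 : 2 : 2. The consultation counts are planned maxima and attendance may be lower. All consultations are planned within about the first 6 months, so the imbalance is confined to that period.

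**2. Size under stated assumptions**

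Inputs, none of them from the protocol:
- p = 0.30, the true 6-month risk in every arm
- q = the share of events caught by the routes common to all arms (questionnaire and coordinator)
- k = the share recorded at a consultation: 0 in control, 0.40 with 6 visits, 0.60 with 12 visits, independent of q

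Observed risk = p × [1 − (1 − q)(1 − k)].

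With q = 0.50:
- Control: 0.30 × 0.50 = 15%
- Exercise: 0.30 × (1 − 0.50 × 0.60) = 21%
- Combined: 0.30 × (1 − 0.50 × 0.40) = 24%
- Gaps: 6 and 9 points against control, and 3 points between the active arms

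With q = 0.90:
- Control: 0.30 × 0.90 = 27.0%
- Exercise: 0.30 × (1 − 0.10 × 0.60) = 28.2%
- Combined: 0.30 × (1 − 0.10 × 0.40) = 28.8%
- Gaps: 1.2 and 1.8 points against control, and 0.6 points between the active arms

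A second parametrisation lets each clinician stream (physiotherapist, dietitian) capture a share c independently. The combined-to-control ratio is then [1 − (1 − q)(1 − c)²] / q.
- q = 0.50, c = 0.50: 0.875 / 0.50 = 1.75
- q = 0.90, c = 0.25: 0.944 / 0.90 = 1.05

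The ratio is 1.00 only if the common routes catch every event (q = 1) or consultations add nothing (c = 0). The direction therefore holds across the range, while the size depends strongly on q.

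**The case against.** The strongest reply is that the protocol specifies no pooled harms table and no test of harms. The Additional measures text says how events are collected, not how they are analysed, and tabulation by source is ordinary analysis-plan detail. Consultation notes and questionnaires are also separate records, so separation by source may still be possible. Table 4 places harms at the two questionnaire time points, which fits a questionnaire-based summary without establishing one.

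Much of this stands. A reader might infer that a biased between-arm test is planned, but the Analysis section does not support that. A reader might also infer that events in controls go uncollected. They do not: controls have both questionnaires and the coordinator route, and what they lack is clinician recording. What remains is that the protocol itself defines the measure from sources unequal by arm, and nothing in it separates them or limits comparison to the shared source.

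The independence assumption is also open to challenge. If events told to a clinician tend to be those later recalled, the gap shrinks. With q = 0.50 and the fullest possible overlap, Exercise would equal control at 15%, and combined would be 0.30 × 0.60 = 18%.

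Finally, a questionnaire-only comparison is less sensitive to early transient effects. That is a real cost, and the fix has to address it.

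**Conclusion.** The point holds as a weakness in the stated harms measure. A by-arm count pooled over all sources would be expected to overstate harm in the active arms against control, and in the combined arm against Exercise, during about the first 6 months, unless the common routes catch every event.

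With a 30% true risk, 40% or 60% independent capture at consultations, and common routes catching 50% to 90% of events, the gap is about 1 to 9 points against control. Between Exercise and combined it is about 0.6 to 3 points. These inputs are assumptions that the protocol neither supports nor contradicts.

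It would be tempting to take the upper end as the expected bias, or to say that the reported counts are bound to differ. Neither follows: the upper end is one scenario, and the difference is one of expectation. The efficacy outcomes and the sample size are not affected.

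**What to change.** Add to the protocol or the analysis plan:
1. The source of each adverse event (questionnaire, clinician, coordinator) is recorded in the event log.
2. Any between-arm comparison of harms uses the events from the 6- and 12-month questionnaires, which are collected identically in all arms.
3. Clinician- and coordinator-reported events are tabulated separately by arm and source, descriptively, with the number of planned consultations per arm stated.
4. Serious events are reported from all sources.

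The cost is one data field and a few lines of text. No data are discarded, and safety reporting does not change. The downside is that the questionnaire comparison rests on fewer events and may under-count early transient effects, including those expected in the first week of the diet. For that reason the clinician-reported table must be shown beside it and not dropped.
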